## Background

Multilevel spinal fusion surgery has typically been associated with significant blood loss and transfusion requirements. Significant patient factors affecting operative blood loss include duration of exposure, severity and type of spinal deformity, and patient height [1-3]. Surgery dependent factors include operating time, procedure performed, combined anterior/posterior approaches, number of vertebrae fused, number of anchors placed, average mean arterial pressure (MAP) during surgery, blood salvage techniques, and the use of anti-fibrinolytic medications [4]. Factors with an unclear role include, but are not limited to: pre-operative hemoglobin, autologous donation, history of coagulopathy, prior use of anticoagulant medication, and type of fibrinolytic medication used in the operating room.

Large quantities of intra-operative and postoperative blood loss require blood transfusion to maintain tissue perfusion and prevent end-organ damage. The use of allogenic blood, however, confers an additional risk for blood borne pathogens. Also noteworthy is the risk for transfusion related reactions, immune suppression, and a decrease in coagulation factors. There is also evidence that transfusion of allogenic blood is increasingly harmful as more blood is transfused [5]. While the innovation of autologous transfusion, cell-salvage, and pre-operative erythropoietin administration has reduced the need for allogenic transfusion, patients undergoing spinal fusion may lose up to their entire blood volume or more for highly complex spinal reconstructive procedures [6].

More recently the use of anti-fibrinolytics has come into favor for cardiac and orthopedic surgery where blood loss is of significant concern. These include aprotinin, tranexamic acid (TXA), and epsilon aminocaproic acid (EACA, trade name Amicar?). Aprotinin is a serine protease inhibitor with anti-fibrinolytic properties. In contrast, TXA and EACA are synthetic lysine analogs that act as inhibitors of fibrinolysis. TXA is ten times more potent than EACA and binds more strongly to the plasminogen molecule [7].

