**NMS**	
Inclusion	Exclusion
1. Between 10 and 80 years of age	1. Congenital and syndromic scoliosis
	2. Previous corrective spinal surgery that is being revised

The maximum total number of patients enrolled will be 150 of AIS (50 in each treatment arm), 90 for NMS (30 in each treatment arm), 150 for AD (50 in each treatment arm). These numbers were estimated by critically reviewing the existing spine and cardiac literature comparing TXA and EACA against placebo [6-20]. A power analysis was conducted using the literature to determine the number of patients necessary to attain significant results (Tables 2 and 3).

**Table 2 T2:** Power study to determine number of patients needed in AIS group.

	TXA		Amicar		Control		
	**Blood loss**	**Standard Deviation**	**Blood Loss**	**Standard Deviation**	**Blood Loss**	**Standard Deviation**	**Sample Size Needed**

Intra-op blood loss	1072 mL	+/- 425 mL	-	-	1420 mL	+/- 644 mL	58

Intra-op blood loss	1072 mL	+/- 425 mL	893 mL	+/- 220 mL	-	-	80

Total blood transfused	1253 mL	+/- 884 mL	-	-	1784 mL	+/- 733 mL	55

Total units transferred	-	-	1.2 U	+/- 1.1 U	2.2 U	+/- 1.3 U	34

**Table 3 T3:** Power study to determine number of patients needed for NMS group

	TXA		Amicar		Control		
	**Blood loss**	**Standard Deviation**	**Blood Loss**	**Standard Deviation**	**Blood Loss**	**Standard Deviation**	**Sample Size Needed**

Intra-op blood loss	1408 mL	+/- 605 mL	-	-	2690 mL	+/- 1266 mL	14

Intra-op blood loss	1976 mL	+/- 860 mL	1117 mL	+/- 718 mL	-	-	30

Total blood transfused	808 mL	+/- 531 mL	-	-	1391 mL	+/- 723 mL	34

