An analysis of variance, univariate, and multivariate logistic regression analysis will be used to analyze the difference in outcomes. Odds ratios will be calculated regarding the risk for autologous or allogenic transfusion both intra and postoperatively. P-values will be calculated regarding the relative blood loss in the intra and postoperative periods as well. The groups will be analyzed to characterize the homogeneity of their pre-operative characteristics that may influence blood loss. Patients with AIS, NMS or AD will be stratified by primary diagnosis and analyzed separately but also collectively accounting for patient and surgery-related confounders. Non-continuous data will be analyzed with a non-parametric test. Pre-operative curve characteristics including Cobb angle and number of vertebrae fused will be categorized to ensure similar groups for comparison.

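### Categorizing Cobb angle and fusion length cannot make the arms similar; adjusting for the measured values in every blood-loss comparison would remove more chance imbalance and more variance

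*Protocol article*

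**What the plan says.** Three statements under Statistical considerations in the protocol article bear on this.

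- Handling of the two factors: "Pre-operative curve characteristics including Cobb angle and number of vertebrae fused will be categorized to ensure similar groups for comparison". This is the only handling stated for them.
- Baseline comparison: "The groups will be analyzed to characterize the homogeneity of their pre-operative characteristics that may influence blood loss". No test, significance level or threshold is attached.
- Outcome analysis: "An analysis of variance, univariate, and multivariate logistic regression analysis will be used to analyze the difference in outcomes". The diagnoses are to be "analyzed separately but also collectively accounting for patient and surgery-related confounders".

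The Background lists severity of deformity among the patient factors for blood loss, and "number of vertebrae fused, number of anchors placed" among the surgical ones. Patient selection caps enrolment at "150 of AIS (50 in each treatment arm), 90 for NMS (30 in each treatment arm), 150 for AD (50 in each treatment arm").

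**The concern.** The stated purpose and the stated method do not fit. Similarity of the arms comes from the allocation. Medication Supply and Randomization describes computer-generated assignment and mentions no stratification on either factor. Cutting a measured variable into classes after that does nothing to the arms; it only makes them look more alike, because differences within a class no longer show. The usual protection against chance imbalance in a prognostic factor is adjustment fixed in advance, and it works best on the measured scale.

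Two things are at stake in the blood-loss comparisons. One is the part of a chance imbalance that stays in the treatment contrast. The other is outcome variance that these factors could have explained, which is lost whether or not the arms are imbalanced. The second works against the plan's own wish, in the same section, to keep the variance of blood loss low.

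**Working it through.** The article gives no figure on baseline balance, so there is none to reproduce.

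**Inputs**
- From Patient selection: 50 per arm (AIS, AD) and 30 per arm (NMS).
- From Table 2 (AIS, TXA against EACA): 1072 mL (SD 425) and 893 mL (SD 220).
- Assumed, because not stated: 2, 3 or 4 equal-sized categories; a normally distributed factor; a linear relation with blood loss; correlation ρ of 0.3 to 0.6.

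**1. Information kept by categories.** For k equal-sized groups of a normal variable, the share of its variance kept, R, is the variance of the group means. For k = 2 the group means are ±0.798, so R = 0.798² = 2/π = 0.637. For k = 3, R = 0.793. For k = 4, R = 0.861.

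**2. Bias left after adjusting for the categories.** The share left is 1 − R in the limit of a small imbalance; the second figure is for a 0.5-SD shift.

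| Categories | 1 − R | 0.5-SD shift |
|---|---|---|
| 2 | 36.3% | 36.5% |
| 3 | 20.7% | 20.3% |
| 4 | 13.9% | 13.5% |
| Measured value | 0% | 0% |

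**3. Residual variance relative to adjusting for the measured value.** The ratio is (1 − Rρ²)/(1 − ρ²). For k = 2 and ρ = 0.5 it is (1 − 0.637 × 0.25)/0.75 = 0.841/0.75 = 1.12.

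| ρ | 2 categories | 3 | 4 |
|---|---|---|---|
| 0.3 | +4% | +2% | +1% |
| 0.5 | +12% | +7% | +5% |
| 0.6 | +20% | +12% | +8% |

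A 12% rise acts like a smaller trial: 50/1.12 ≈ 45 and 30/1.12 ≈ 27 patients per arm.

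**4. How often a large imbalance arises.** The difference in means of a standardized factor between two arms has standard error √(2/n): 0.20 SD at n = 50 and 0.26 SD at n = 30. A difference of at least 0.5 SD therefore occurs with probability 1.2% (z = 2.50) or 5.3% (z = 1.94), per pair of arms and factor.

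**5. Size in millilitres, as an illustration.** With the Table 2 SDs, the common SD is √((425² + 220²)/2) = 338 mL. A 0.5-SD imbalance with ρ = 0.5 shifts the unadjusted contrast by 0.5 × 0.5 × 338 = 85 mL. After adjustment for two, three or four categories, about 31, 17 or 12 mL remain (85 mL times 0.363, 0.207 or 0.139), against a planned difference of 1072 − 893 = 179 mL.

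**The case against.** The strongest reply is that the plan does adjust. It names multivariate regression and a pooled analysis accounting for confounders, and it does not say that categories replace measured values in those models. A condensed article may also leave cut-points and covariate scale to a fuller document. Much of this stands: the absence of cut-points is no finding, and it would be wrong to say that the plan categorizes in place of adjusting. What remains is what the article does state. It gives categorization a purpose that it cannot serve. The regression it names is logistic, which suits the transfusion odds; for continuous blood loss it names analysis of variance and p-values. The clause on confounders reads most naturally as attached to the pooled analysis.

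Three stronger readings are tempting and are not supported.

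- *A balance test will pass imbalanced arms as similar.* A reader might compute that a 5% test after a median split misses a 0.5-SD shift about 42% of the time at 50 per arm and 61-62% at 30. But the homogeneity analysis is only to characterize the groups, in a separate sentence, with no test or rule. The measured value would also miss 30% and 52%, so most of that is small-sample power. In the pooled data, at 130 per arm, tests on two to four categories miss 4-12%.
- *A third of the bias remains.* This needs two categories and an analysis that adjusts for them. A balance check alone removes nothing.
- *Type I error is inflated.* At ρ = 0.5, the unadjusted test rejects 8-9% of the time when the baseline p-value lies between 0.05 and 0.20. That is a selected band. Over all non-significant baselines the rate is 4.3%, and unconditionally it is 5.0%.

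**Conclusion.** The point holds in a limited form. Categorizing these two factors cannot ensure similar arms, and it discards information on variables that the article itself ties to blood loss. If the categories are adjusted for, 13-36% of the bias from a chance imbalance stays (four down to two categories). Residual variance is 1-20% higher than with the measured value over the assumed correlations of 0.3 to 0.6. These figures rest on a normal factor, a linear relation and equal-sized categories.

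Under randomization this is conditional bias and lost precision. It matters most in the comparisons within a diagnosis, where the arms are small and adjustment is not clearly stated. It does not threaten the validity of the trial, but the better method is nearly free.

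**What to change.** Under Statistical considerations, replace the categorizing sentence with a pre-specified linear model (ANCOVA) for blood loss. Include pre-operative Cobb angle, where it applies to the diagnosis, and the planned number of levels to be fused as continuous covariates. Use the planned number because it is fixed before the infusion starts. Fit the model within each diagnosis and in the pooled analysis, whatever balance is observed; a low-order spline can be used if linearity is in doubt. Describe baseline factors by arm (mean, SD, standardized difference), and state that this description does not decide whether to adjust.

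The cost is a change of analysis wording and one or two degrees of freedom per covariate. No new data should be needed: Investigation schedule and follow-up already records the intended procedure before surgery, and the present sentence presupposes that Cobb angle is recorded.

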## Discussion

Overall, orthopedic studies have demonstrated the efficacy of TXA and EACA over placebo in relation to blood loss [8-16]. However, the specifics of this demonstrated benefit are lacking. In particular, a reduction in intra-operative blood loss has been inconsistently reported. In two recent Cochrane reviews, TXA was noted to be more efficacious than EACA at reducing total blood loss, but neither drug significantly reduced intra-operative bleeding [7,8]. The most recent review demonstrated a reduction in transfusion volume with antifibrinolytic medications in scoliosis surgery, but could not comment on the benefit of one medication over another [7,8]. In addition, studies solely reporting intra-operative blood losses may have overlooked postoperative benefits. The authors concluded that antifibrinolytic treatments have greatest efficacy in controlling postoperative bleeding, but also that more investigation was needed. Comparing trials in all surgical fields including cardiac surgery, TXA - but not EACA - was found to reduce the transfusion rate over placebo.

The cardiac literature has produced seven prospective studies comparing TXA and EACA head-to-head, but no trial was assessed as having proper patient randomization and physician blinding [7,18-20]. Moreover, for five of the seven trials the method of randomization raised uncertainty for the reviewers [7]. In addition, the trials were inappropriately powered to detect differences between TXA and EACA and excluded high-risk patients to accentuate differences between the two drugs.

The role of anti-fibrinolytics to manage blood loss, therefore, remains largely surgeon dependent and is not the standard of care in spinal deformity surgery. Of the scoliosis studies examined in the Cochrane review, only two studies adequately randomized patients and blinded both the surgeon and anesthesiologist to the patient's treatment [8]. Since operative blood loss is partly dependent upon surgical and anesthetic conditions, proper physician blinding is imperative. As stated, no single orthopedic study has prospectively compared the relative efficacy of TXA and EACA head-to-head.

The goal of this proposal is to perform a randomized, prospective, double blind study comparing the relative efficacy of TXA, EACA, and controls in AIS, NMS, and AD patients. AIS patients are particularly well suited to investigate because these patients are generally healthy, and free from use of anticoagulant medications. These factors all help to minimize the effect of known confounders effecting blood loss. Patients with NMS, however, have a heterogonous profile and often have multiple confounding medical problems that may affect blood loss. Typically these patients have significant larger blood loss and transfusion needs as compared to AIS patients. However, this difference may accentuate differences in blood loss for TXA versus EACA. Finally, AD patients represent the largest subgroup of spinal deformity patients. Their inclusion into this study allows for the results to have a broader application across spinal deformity patients.

We hope that this study will determine if a difference in efficacy exists between TXA, EACA and placebo and begin to establish a new standard of care in corrective spinal surgery. The use of patient populations beyond those of AIS may have meaningful results that can be applied to a wider range of patients undergoing corrective spinal procedures by reducing morbidities associated with blood loss.
